## Abstract

**Background:**

New-onset diabetes mellitus after transplantation (NODAT), a frequent and serious complication after transplantation, is associated with decreased graft and patient survival. Currently, it is diagnosed and treated primarily according to existing guidelines for type II diabetes. To date, only a few trials have studied antidiabetic drugs in patients with NODAT. Vildagliptin is a novel dipeptidyl peptidase-4 (DPP-4) inhibitor that improves pancreatic islet function by enhancing both α- and β-cell responsiveness to increased blood glucose. Experimental data show potential protective effects of DPP-4 inhibitors on islet function after exogenous stress stimuli including immunosuppressants. Therefore, the therapy of NODAT with this class of compounds seems attractive. At present, vildagliptin is used to treat type II diabetes as monotherapy or in combination with other antidiabetic drugs, since that it efficiently decreases glycated hemoglobin (HbA1c) values. Additionally, vildagliptin has been shown to be safe in patients with moderately impaired kidney function. This study will evaluate the safety and efficacy of vildagliptin monotherapy in renal transplant recipients with recently diagnosed NODAT.

**Methods/Design:**

This study is a randomized, placebo-controlled, double-blind, prospective phase II trial. Using the results of routinely performed oral glucose tolerance tests (OGTT) in stable renal transplant patients at our center, we will recruit patients without a history of diabetes and a 2 h glucose value surpassing 200 mg/dl (11.1 mmol/l). They are randomized to receive either 50 mg vildagliptin or placebo once daily. A total of 32 patients with newly diagnosed NODAT will be included. The primary endpoint is the difference in the 2 h glucose value between baseline and the repeated OGTT performed 3 months after treatment start, compared between the vildagliptin- and the placebo-group. Secondary endpoints include changes in HbA1c and fasting plasma glucose (FPG). The safety of vildagliptin in renal transplant patients will be assessed by the number of symptomatic hypoglycemic episodes (glucose <72 mg/dl or 4 mmol/l), the number of adverse events, and possible medication-associated side-effects.

**Discussion:**

NODAT is a severe complication after kidney transplantation. Few trials have assessed the safety and efficacy of antidiabetic drugs for these patients. The purpose of this study is to assess the safety and efficacy of vildagliptin in renal transplant patients with NODAT.

**Trial Registration:**

ClinicalTrials.gov NCT00980356

## Background

New-onset diabetes after transplantation (NODAT), also called post-transplant diabetes mellitus (PTDM), remains a severe metabolic complication in patients after organ transplantation. NODAT leads to an increased incidence of cardiovascular disease (CVD) and consequently reduced graft and patient survival [1,2]. In non-transplanted patients, diabetes mellitus (DM) has been identified as a major independent risk factor for CVD [3]. CVD includes atherosclerotic coronary heart disease, heart failure, myocardial infarction, stroke and peripheral vascular disease [4]. Patients with CVD and DM suffer from a worse prognosis for survival than patients without these conditions. In organ transplant recipients, mortality due to CVD remains the most common cause of mortality [1]. In renal transplant recipients NODAT is associated not only with increased cardiovascular morbidity and mortality, but also with impaired long-term graft function and increased risk of graft loss [4,5]. Hence, NODAT needs medical attention and treatment and therefore clinical trials with antidiabetic drugs for the therapy of NODAT remain of high interest.

The reported incidence of NODAT varies between 2 and 53%. This high variability is due the lack of a standard definition in clinical studies [6]. Some reports define NODAT by the requirement for exogenous insulin without further examinations, such as an oral glucose tolerance test (OGTT). Currently, the diagnosis of NODAT is based on guidelines for type II diabetes (T2DM) from the American Diabetes Association (ADA), which include impaired glucose tolerance (IGT) and impaired fasting glucose (IFG) as diagnostic parameters [7]. Development of NODAT has modifiable (e.g. body weight, immunosuppressive drug therapy) and non-modifiable (e.g. age, ethnicity, polycystic kidney disease) risk factors [8]. The role of immunosuppressants (e.g. corticosteroids or calcineurin inhibitors (CNIs)) in the clinical course of diabetes is clearly established, and disease development is probably mediated by an increased beta-cell apoptosis and impaired insulin sensitivity [4,9]. The incidence of steroid-induced diabetes is related to the treatment duration and the dose of corticosteroids [10]. Some authors propose steroid reduction or complete withdrawal as a means to reduce the incidence of NODAT, but steroid withdraw has been associated with an increased risk for graft rejection [4].

Most centers currently follow so-called "step-up" strategies established for the treatment of T2DM starting with non-pharmacological therapies and life-style modification, subsequently followed by oral antidiabetic therapy and finally insulin [4]. Pharmacodynamic and pharmacokinetic drug properties may be altered in patients with renal impairment and new drugs have to be studied regarding safety and effectiveness in patients with impaired renal function. In renal transplant patients, drugs are at additional risk of interacting with immunosuppressive agents as well as with other co-medications [11].

Vildagliptin, a dipeptidyl peptidase IV (DPP-4) inhibitor that, belongs to a new class of oral antidiabetic drugs [12]. DPP-4 inhibitors enhance the activity of incretin hormones in response to a glucose load by blocking the hormones responsible for incretin degradation [13]. Incretins are gut hormones that are secreted from enteroendocrine cells into the blood within minutes after food intake. The incretin hormones *glucose-dependent insulinotropic polypeptide *(GIP) and *glucagon-like peptide-1 *(GLP-1) have been reported to exert numerous metabolic effects contributing to the regulation of blood glucose levels [14]. Vildagliptin decreases glycated hemoglobin (HbA1c) in patients with T2DM when given as monotherapy or combined with metformin or glitazones [15-19]. Furthermore, vildagliptin has been shown to be safe in patients with mild to moderately impaired kidney function [20].

This study aims to assess the safety and efficacy of vildagliptin in patients with NODAT.

## Methods/Design

### Hypothesis

Vildagliptin improves glucose metabolism in patients suffering from newly diagnosed NODAT.

### Objectives

This 16-week trial aims to evaluate the safety and efficacy of vildagliptin in stable renal transplant recipients with newly diagnosed NODAT.

The primary outcome parameter will be the difference in 2 h glucose levels obtained during an OGTT between stable renal transplant patients receiving vildagliptin or placebo after 3 months treatment.

The secondary study outcomes will include change in HbA1c and fasting plasma glucose after three months of treatment, the safety of vildagliptin in renal transplant recipients regarding kidney function, liver function and the potential for drug-drug interactions with immunosuppressive medications (Intention to treat (ITT) analysis), the safety of vildagliptin for glycemic control in patients with impaired kidney function, and the long-lasting effects of vildagliptin on β-cell function one month after treatment stop.

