### Statistical analysis plan

The statistical analysis plan (SAP) provides full details regarding the analyses, the data display, and the algorithms to be used for data derivations. The SAP includes the definition of major and minor protocol deviations which will be identified by medically trained staff before the study closure. Safety and tolerability are analyzed descriptively. Safety analysis is performed on the ITT population.

The study sample will consist of 32 patients with newly diagnosed NODAT. For the primary endpoint analysis, we will assess the differences between treatment and control group in the 2 h glucose value obtained during an OGTT (75 g glucose) after 3 months of vildagliptin or placebo treatment. Based on a two-sided testing and a standard deviation of 20% in relative changes of 2 h OGTT glucose values, α = 0.05 and ß = 0.2, a sample size of 16 patients per group can detect a minimal difference in serum glucose level of 20 mg/dl at the 2 hour time point of the OGTT when comparing baseline levels to levels on day 90. The "Last observation carried forward" (LOCF) method will be used for missing data.

Two different analysis sets are defined for safety and efficacy, respectively. The efficacy of vildagliptin is assessed in all subjects who received the study drug (at least one dose) and did not violate the protocol in a way that might affect the evaluation of the effect of the study drug(s) on the primary objective, i.e. without major protocol violations. The per-protocol set is employed in the analysis of efficacy variables. A sensitivity analysis will be performed for efficacy with the ITT population.

The safety analysis set includes subjects who were randomized and received at least one dose of the study drug (modified intention to treat). The safety set is employed in the analysis of tolerability and safety variables. Statistical analysis is performed with SPSS.

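### The primary outcome is defined both as a change from baseline and as a month-3 level; state one definition, on one scale, compared with baseline as a covariate.

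*Protocol article*

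**What the plan says.** The protocol article describes the primary variable in four places.

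- **Abstract, Methods/Design:** "The primary endpoint is the difference in the 2 h glucose value between baseline and the repeated OGTT performed 3 months after treatment start", then compared between the arms. This is a change score.
- **Objectives:** "the difference in 2 h glucose levels obtained during an OGTT between stable renal transplant patients receiving vildagliptin or placebo after 3 months treatment". This is a month-3 level; baseline is not mentioned.
- **Statistical analysis plan section, analysis sentence:** "differences between treatment and control group in the 2 h glucose value obtained during an OGTT (75 g glucose) after 3 months" of treatment. Again a level.
- **Same section, sample-size sentence:** it assumes "a standard deviation of 20% in relative changes of 2 h OGTT glucose values", concludes that "a sample size of 16 patients per group can detect a minimal difference in serum glucose level of 20 mg/dl", and ends "when comparing baseline levels to levels on day 90". This is a change, with the SD in percent and the target in mg/dl.

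No test, model or covariate is named for the primary comparison. The section refers full analysis details to a SAP that is not shown. Table 1 sets an entry threshold of 200 mg/dl for the 2 h value.

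**The concern.** The Statistical analysis plan section powers the trial on a change and then describes an analysis of a level, and the Abstract and Objectives split the same way. The primary p-value comes from whichever variable is analysed. With 16 patients per arm, chance baseline imbalance feeds into the two versions differently: the level carries whatever part of it persists to month 3, while the change score subtracts all of it. If both remain available, the conclusion can depend on which is taken, and the type I error of the better of the two exceeds 5%. The mixed scales add to this, because the stated sample size cannot be tied to either version.

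**Working it through.** **1. The plan's own figure.** Inputs from the Statistical analysis plan section: two-sided α = 0.05, power 0.80, 16 per group, difference 20 mg/dl, SD 20% of relative change. Normal approximation: n per arm = 2(1.960 + 0.842)² × (SD/difference)².

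- SD equal to the difference (20 mg/dl against 20 mg/dl, or 20 percentage points against 20%): 2 × 7.85 × 1 = 15.7, so 16. Power at 16 is 0.81 (0.78 with the t distribution).
- Inputs as written, at the lowest eligible baseline: SD = 0.20 × 200 = 40 mg/dl, so n = 2 × 7.85 × 4 = 62.8, or 63 per arm. Power at 16 per arm is 0.29.

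The stated 16 is therefore reproduced only if both quantities are on one scale and equal. Steps 2 and 3 use SD of change = 20 mg/dl.

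**2. Level against change, baseline not truncated.** Let r be the baseline-to-month-3 correlation (assumed; the document gives none), with equal variances σ². Var(level) = σ² and Var(change) = 2(1 − r)σ².

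| r | n per arm, level | n per arm, change | power at 16, level | power at 16, change |
|---|---|---|---|---|
| 0.3 | 12 | 16 | 0.92 | 0.81 |
| 0.5 | 16 | 16 | 0.81 | 0.81 |
| 0.7 | 27 | 16 | 0.59 | 0.81 |

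Simulation (20,000 trials per setting, t-tests, assumed baseline mean 240 mg/dl) compared level, absolute change and relative change. Under a true 20 mg/dl effect, the three disagreed on significance in 21%, 25% and 39% of trials at r = 0.3, 0.5 and 0.7. Under no effect, at least one was significant in 8.9% to 9.6%. A rerun with level and absolute change only gives 21%, 25% and 38%, and 8.6% to 9.5%. Nearly all the disagreement is thus level against change.

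**3. Level against change, baseline truncated.** Entry requires at least 200 mg/dl, so baseline is cut from below. I assumed a bivariate normal with slope β and baseline kept above 0, 0.5 or 1 SD, which leaves a fraction v = 0.36, 0.27 or 0.20 of its variance. Repeating the simulation with SD of change still 20 mg/dl, level and change disagree in 11% to 23% of trials under the 20 mg/dl effect. Under no effect, at least one is significant in 7.0% to 8.5%.

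**4. Gain from ANCOVA with a truncated baseline.** In units of the untruncated variance: Var(ANCOVA) = 1 − β²; Var(change) = 1 − β² + (1 − β)²v; Var(level) = 1 − β² + β²v. Gain in patients per arm = 16 × (variance ratio − 1), shown for v = 0.20 to 0.36.

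| β | gain over change | gain over level |
|---|---|---|
| 0.3 | 1.7 to 3.1 | 0.3 to 0.6 |
| 0.5 | 1.1 to 1.9 | 1.1 to 1.9 |
| 0.7 | 0.6 to 1.0 | 3.1 to 5.6 |

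Estimating the slope costs a variance factor of about 1 + 1/(2 × 16 − 4) = 1.036, or 16 × 0.036 ≈ 0.6 patient per arm. At the bottom of these ranges the net gain is about nil.

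**5. Why ANCOVA removes the conflict.** With baseline B as covariate, regressing month-3 glucose Y or the change Y − B on treatment and B gives the same treatment coefficient. Only the coefficient of B differs, by 1.

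**The case against.** **The SAP may settle it.** It is said to hold full details and may already name ANCOVA, so the absence of a model from the article is not an error, and baseline adjustment is a recommendation. This stands. But an unseen SAP can only choose between the two definitions; it cannot make the article's statements agree.

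**The two versions target the same effect.** Under randomisation the expected between-arm difference is the same for level and for change. That is true, and it limits the conflict to which variable is tested and with what variance. At 16 per arm that is enough to change the conclusion.

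**Blinding protects against choosing.** The trial is double-blind and unblinding follows the end of the complete trial. This lowers the risk provided the choice is fixed by then; the article itself does not fix it.

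**Stronger readings that the article does not support.**
- A reader might count three outcomes. Relative change appears only as the scale of the planning SD and is never named as an outcome.
- A reader might say that baseline is ignored throughout. A change score uses baseline by subtraction; what is not named is covariate adjustment.
- A reader might argue that truncation at 200 mg/dl makes a change score over-correct more. Under a linear relation, selection on baseline leaves the slope unchanged and shrinks the penalty (1 − β)²v.
- The equal-variance ratio (1 + r)/2 suggests a gain over change of 3 to 9 patients per arm (16/0.85 = 18.8 to 16/0.65 = 24.6). That ignores the truncated baseline; step 4 gives 0.6 to 3.

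**Conclusion.** The point holds as a contradiction about the primary variable: change in the Abstract and the sample-size sentence, level in the Objectives and the analysis sentence, with planning inputs on mixed scales. It should be corrected.

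Level and change would disagree on significance in about 11% to 23% of trials with a truncated baseline, and 21% to 38% without truncation. These rates assume a true effect of 20 mg/dl, an SD of change of 20 mg/dl, and slopes or correlations of 0.3 to 0.7. The article gives no correlation or baseline spread, so they show the order of magnitude and are not estimates for this trial.

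The main reason for ANCOVA is that it makes the choice between level and change irrelevant. Added precision is secondary and may be close to zero at some of the assumed values.

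**What to change.** Use one definition in the Abstract, the Objectives and the Statistical analysis plan section, fixed before unblinding. The outcome is month-3 2 h OGTT glucose in mg/dl, compared by ANCOVA with treatment as factor and baseline 2 h glucose as covariate, and reported as an adjusted difference with 95% CI. Keeping mg/dl matches the stated 20 mg/dl target; a log-scale ratio would depart from it. Restate the sample-size sentence with SD and target difference on that same scale.

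No new data are needed, because the baseline OGTT is an entry criterion. The cost is one residual degree of freedom and a documented amendment. It is more than an edit of wording, since recruitment began in February 2010 and the trial is already approved and registered.

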### Study design and setting

This study is a prospective, single-center, double-blind, randomized, placebo-controlled, phase II trial in patients with newly diagnosed NODAT. Patient recruitment and follow-up are conducted at the Medical University of Vienna. The study recruitment has started in February 2010.

### Study setting

Patients with a stable kidney allograft, more than 6 months after transplantation, without a history of T1DM or T2DM routinely undergo an OGTT at our outpatient department. All patients with a pathological OGTT (serum glucose levels ≥ 200 mg/d (11.1 mmol/L)) are classified as patients suffering from NODAT. 32 Patients eligible for the study are invited to the outpatient clinic and therapeutic options are discussed. Patients who are willing to take part in the study and have signed their informed consent form are randomized in a 1:1 ratio into study arm A (vildagliptin) or study arm B (placebo). The detailed study flow chart and an overview of study procedures are depicted in Figure 1 and 2, respectively.

**Figure 1 F1:**
[figure not shown]
**Flowchart of the Study**.

**Figure 2 F2:**
[figure not shown]
**Study procedures**. OGTT, oral glucose tolerance test.

### Study intervention

Patients will receive their study medication (vildagliptin or placebo) with instructions to take it once daily 30 minutes before breakfast. Patients will receive continuous counseling on lifestyle modification (e.g. diet, physical exercise) until the end of the study. Participants in the study have to be on a triple immunosuppressive therapy consisting of a CNI (tacrolimus or cyclosporine A), prednisolone, and mycophenolic acid, either as the prodrug (mycophenolate mofetil) or as delayed-release mycophenolic sodium. All changes in concomitant medication will be recorded. Patients will have a visit at our outpatient clinic during weeks 2, 4, 8, 12, and 16 (Figure 2). At each visit, blood samples are collected to determine blood parameters including complete blood count, serum chemistry, C-reactive protein, creatinine, calculated glomerular filtration rate (cGFR) using the "Modification of Diet in Renal Disease" (MDRD) formula, potassium, sodium, phosphate, chloride, calcium, total bilirubin, ALAT, ASAT, total protein, LDL, HDL, triglycerides. Patients with a cGFR between 30 and 50 mL/min./1.73 m^2 ^will have weekly blood checks comprising creatinine and ASAT/ALAT during the first month for safety reasons. Each patient is expected to parcipate in the study for 120 days. Unblinding of the study will be performed after the end of the complete trial. Patients whose OGTT did not improve 4 months after study start will be treated by the physicians of our outpatient clinic according to the guidelines.

### Informed consent

The investigator explains the nature of the study, its purpose, procedures, expected duration, and the potential risks and benefits associated with study participation along with any discomfort that may be expected. Patients will be informed about the strict confidentiality of their subject data, but also that their medical records may be reviewed for trial purposes by authorized individuals other than their treating physician. Each subject will be informed that study participation is voluntary and withdrawal is possible at any time during the study period. Withdrawal will not prejudice the subject's subsequent care. Subjects are given time to read and understand the statements before signing consent and dating the document. Subjects receive a copy of the signed written statement and the original copy of the informed consent is stored in the investigator study files. No subject is entered into the study until informed consent has been obtained.

### Safety assessments

Safety assessments will include the monitoring and recording of all adverse events (AE), including serious adverse events (SAE). An AE is any undesirable experience associated with the use of a medical product in a patient. An SAE is defined as any untoward medical occurrence that at any dose results in death, is life-threatening, requires inpatient hospitalization or prolongation of existing hospitalization, or results in persistent or significant disability/incapacity. The most probable AEs caused by vildagliptin are consistent with the known side-effects, which are the cause of the previously described exclusion criteria (table 1), such as wound healing disorders or severe renal impairment. The interruption or premature discontinuation of the study drugs might be triggered by AE, diagnostic or therapeutic procedures, abnormal laboratory values (e.g. basal ASAT/ALAT 50% elevated or more, serum creatinine 25% elevated or more) and for administrative reasons, in particular the withdrawal of the patient's consent.

**Table 1 T1:** Patients inclusion and exclusion criteria of the study.

INCLUSION CRITERIA	EXCLUSION CRITERIA
≥18 years	Patients with prior **history of type 1 or type 2 diabetes**
	
Newly diagnosed **NODAT **defined by pathologic OGTT (2 h, 75 mg glucose): glucose ≥200 mg/dL	**Body mass index **(BMI) **> 40 kg/m^2^** - **Pregnancy**
	
**Renal transplantation **(deceased or living donor) and treatment with the standard immunosuppressionat our center, consisting of a triple therapy with tacrolimusor cyclosporine A, mycophenolatemofetil, and prednisone	**Severe renal impairment **(GFR < 30 mL/min./1.73 m^2^)
	
**Stable graft function **for more than 6 months post transplant	**Severe liver impairment **(ASAT/ALAT levels over threefold elevated compared to reference values)
	
**Informed consent **of the patient	Severe blood glucose elevation with the need for **insulin therapy **or

### Statistical analysis plan

The statistical analysis plan (SAP) provides full details regarding the analyses, the data display, and the algorithms to be used for data derivations. The SAP includes the definition of major and minor protocol deviations which will be identified by medically trained staff before the study closure. Safety and tolerability are analyzed descriptively. Safety analysis is performed on the ITT population.

The study sample will consist of 32 patients with newly diagnosed NODAT. For the primary endpoint analysis, we will assess the differences between treatment and control group in the 2 h glucose value obtained during an OGTT (75 g glucose) after 3 months of vildagliptin or placebo treatment. Based on a two-sided testing and a standard deviation of 20% in relative changes of 2 h OGTT glucose values, α = 0.05 and ß = 0.2, a sample size of 16 patients per group can detect a minimal difference in serum glucose level of 20 mg/dl at the 2 hour time point of the OGTT when comparing baseline levels to levels on day 90. The "Last observation carried forward" (LOCF) method will be used for missing data.

Two different analysis sets are defined for safety and efficacy, respectively. The efficacy of vildagliptin is assessed in all subjects who received the study drug (at least one dose) and did not violate the protocol in a way that might affect the evaluation of the effect of the study drug(s) on the primary objective, i.e. without major protocol violations. The per-protocol set is employed in the analysis of efficacy variables. A sensitivity analysis will be performed for efficacy with the ITT population.

The safety analysis set includes subjects who were randomized and received at least one dose of the study drug (modified intention to treat). The safety set is employed in the analysis of tolerability and safety variables. Statistical analysis is performed with SPSS.

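### The 80% power is computed on all 32 enrolled patients, but efficacy is analysed per protocol, so the stated power has no margin for any exclusion

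*Protocol article*

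**What the plan says.** The Statistical analysis plan section of the protocol article fixes three things that bear on this point.

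- **Power inputs and sample size.** "Based on a two-sided testing and a standard deviation of 20% in relative changes of 2 h OGTT glucose values, α = 0.05 and ß = 0.2", it states that "a sample size of 16 patients per group can detect a minimal difference in serum glucose level of 20 mg/dl".
- **Enrolment.** "The study sample will consist of 32 patients with newly diagnosed NODAT". The Abstract also gives 32 as the number included. Allocation is 1:1 (Study setting), so 32 is exactly 2 × 16.
- **Analysis set.** "The per-protocol set is employed in the analysis of efficacy variables". That set requires at least one dose of study drug and no major protocol violation. The ITT population serves only as a sensitivity analysis for efficacy. LOCF is named for missing data.

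Elsewhere the article foresees that patients may withdraw or stop study drug. The Informed consent section allows withdrawal at any time. Safety assessments lists triggers for interruption or discontinuation, among them "abnormal laboratory values (e.g. basal ASAT/ALAT 50% elevated or more, serum creatinine 25% elevated or more". The Risk-benefit assessment adds a GFR-based stop.

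Study setting uses the number 32 differently: "32 Patients eligible for the study are invited to the outpatient clinic and therapeutic options are discussed". Only those who then consent "are randomized in a 1:1 ratio into study arm A (vildagliptin) or study arm B (placebo".

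**The concern.** The power is stated for everyone enrolled, while the analysis that decides the trial runs on a subset. Nothing printed links the number enrolled to the number analysed. The 80% therefore applies to a sample that the main analysis reaches only if nobody is excluded.

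At stake is how a null result is read. A negative per-protocol comparison would be reported as coming from a trial with 80% power, although the analysis behind it may have had less. The Study setting sentence adds an inconsistency: 32 can be both the number invited and the number included only if nobody declines.

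**Working it through.** **Inputs.** Alpha 0.05 two-sided, beta 0.2, SD 20% of the relative change, difference 20 mg/dl, 16 per group (Statistical analysis plan); 1:1 allocation (Study setting); entry at "glucose ≥200 mg/dL" on the 2 h value (Table 1). No loss or violation rate is given, so losses of zero to four per arm (0% to 25% of 16) are assumed to show the range.

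**Step 1: reproduce 16 per group.** For two means, n per group = 2(1.96 + 0.8416)² / d², where d is the difference divided by the SD. With d = 1 (for example 20% against an SD of 20%), n = 15.7, rounded up to 16. The noncentral t gives 16.7, so 17. Sixteen is therefore the bare minimum by the normal approximation and one short by the t-test.

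**Step 2: power at d = 1 when fewer are analysed.** Normal approximation: power = Φ(d√(n/2) − 1.96). For n = 16 this is Φ(2.828 − 1.96) = Φ(0.868) = 80.7%.

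| Analysed per arm | Excluded per arm | Normal | t-test | Difference (in SD) for 80% power, t-test |
|---|---|---|---|---|
| 16 | 0 | 80.7% | 78.1% | 1.02 |
| 15 | 1 | 78.2% | 75.3% | 1.06 |
| 14 | 2 (12.5%) | 75.4% | 72.1% | 1.10 |
| 13 | 3 (19%) | 72.2% | 68.7% | 1.15 |
| 12 | 4 (25%) | 68.8% | 64.9% | 1.20 |

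A single exclusion in the whole trial (16 against 15) gives 79.5% by the normal approximation and 76.7% by the t-test. So even the more generous method falls below 80% at the first exclusion.

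**Step 3: separate attrition from method.** With no loss, moving from normal to t costs 80.7 − 78.1 = 2.6 points, which is not attrition. Within one method, two exclusions per arm cost 80.7 − 75.4 = 5.3 points (normal) or 78.1 − 72.1 = 6.0 points (t). Against the stated 80%, the shortfall at 14 per arm is 4.6 or 7.9 points.

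**Step 4: the literal inputs.** Entry at 200 mg/dl or above makes an SD of 20% at least 0.20 × 200 = 40 mg/dl, so d is at most 20/40 = 0.5. Then n = 15.7/0.25 = 62.8, or 63 per group. With 16 per group, power is Φ(1.414 − 1.96) = 29% (t-test 28%); with 14 per group it is 26% (25%). The table in step 2 therefore holds only on the favourable reading of the effect size.

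**The case against.** Several points on the other side stand.

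- **Stopping drug is not leaving the analysis.** The efficacy set excludes undosed patients and major violators. Stops for adverse events, laboratory values or GFR are provided for in the protocol and are not, as written, violations. The definition of a major deviation is left to an SAP that is not shown. A reader might infer that each listed reason for stopping reduces the per-protocol set; the documents do not show that.
- **No loss rate is given.** A reader might conclude that true power is about 65–75%. That range assumes between one and four exclusions in every arm and leaves out zero loss. Only conditional figures are supported.
- **Part of the gap is method.** The 2.6 points between the normal and t results would exist with no loss at all.
- **LOCF.** It fills missing values and does not bring back excluded violators. It is tempting to add that it enters zero change and dilutes the effect. That depends on whether an interim OGTT is done. Study intervention lists none among the visit blood tests, but the procedures overview (Figure 2) is not shown.
- **Study setting.** Read with the Abstract, the Informed consent section and the Statistical analysis plan section, the sentence about inviting 32 is probably loose wording. It does not establish that fewer than 32 will be randomised.

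It can also be said that a condensed article may leave loss allowances or replacement rules to the full protocol. A replacement rule cannot be excluded. But the article itself prints the sample size, the power and the analysis set, and as printed these leave no margin.

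**Conclusion.** The point holds in a limited form. The 80% power is computed for 16 per group, which is the whole enrolment, while the main efficacy analysis is on a per-protocol set that can only be equal or smaller. Any exclusion takes the power below the stated figure.

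The direction is certain; the size rests on two assumptions. One is the number excluded, which the documents do not give. The other is that the difference equals one SD, which the protocol does not state and which is used here only because it reproduces 16 per group. Under both, one exclusion per arm is a small loss (about 2.5 to 3 points), two are clear (5 to 6 points) and four are substantial (about 12 to 13 points).

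The mismatch between a difference in mg/dl and an SD in percent is a separate and larger problem. Allowing for losses alone would not restore 80% power on the literal inputs.

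**What to change.** No additional patients are needed. In the Statistical analysis plan section:

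1. First express the target difference and the SD on one scale, either both in percent or both in mg/dl with the assumed baseline stated.
2. State the assumed proportion excluded from the per-protocol set and the resulting evaluable number per arm.
3. Give the power for the restated target, and the detectable difference, at that evaluable number. For example, with 12–14 evaluable per arm the t-test has 80% power for about 1.1–1.2 SD. With an SD of 20% that is 22–24 percentage points of relative change (1.1 × 20 to 1.2 × 20), or 44–48 mg/dl at a baseline of 200 mg/dl (1.1 × 40 to 1.2 × 40).

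The new text should not print power for a one-SD difference as if that were the protocol's stated target. In Study setting, reword the sentence so that 32 is the number randomised, in agreement with the Abstract and the Statistical analysis plan section.

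The cost is wording only: no new procedures or visits. The sponsor has to commit to a loss assumption, and the printed power or detectable difference becomes less favourable.
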